### Randomisation

Families were randomised upon receipt of their signed consent form and baseline questionnaire. Prior to the recruitment period, a computer generated random number sequence provided by
http://www.random.org was established for each participating LGA. This allowed for each parent or family (if both parents participated) per LGA to have equal chance of being allocated to either of the intervention conditions (i.e., written information with telephone support or written information only) or control condition. The research team and families remained blind to group allocation at the time of recruitment and consent. However, following the return of the participants consent form, knowledge of group allocation is unavoidable given the type of intervention. Thus, each parent or family were allocated to one of the intervention or control conditions and notified of this allocation.

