### Sample size/power calculation

Power analysis using the program 'GPower 3.1.2' was conducted to determine the required sample size for the study. A 3-group comparative study would require a total sample of 184 participants (approximately 61 parents in each treatment condition) to have 80% power to detect a statistically significant finding at *p* < .05 and a moderate effect size for the short-term outcomes at two weeks post-intervention. Allowing for a 20% dropout rate, we aimed to recruit approximately 221 parents (approximately 74 participants in each treatment condition).

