### Data analysis

A range of descriptive and multivariate data analyses will be used to assess the aims of the study. Descriptive statistics will be presented of the demographic characteristics of the sample. Means and standard deviations will be given for continuous outcomes, as well as medians and inter-quartile ranges where continuous data are skewed. Frequencies for categorical data will be reported. A mixed-design analysis of variance (split-plot ANOVA) will be conducted to compare the intervention and control conditions (between-subjects factor) on each of the primary and secondary outcomes at pre, post and follow-up (within-subjects factor). Effect sizes will be reported where appropriate, with 0.01, 0.06 and 0.14 as small, medium and large effect sizes for multivariate *η*^2^, while 0.2, 0.5 and 0.8 are small, medium, and large effect sizes for Cohen’s *d.* Finally, intention-to-treat analysis will be conducted using the last observation carried forward method for the missing post-intervention and follow-up data.

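### Families are allocated, with both partners of a couple in the same arm, but the sample size counts parents and the named split-plot ANOVA has no family term, so p-values are too small wherever partners' outcomes correlate positively.

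*Protocol article*

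**What the plan says.** Under Randomisation, the article states: "Families were randomised upon receipt of their signed consent form and baseline questionnaire". It adds, of the sequence drawn up for each Local Government Area: "This allowed for each parent or family (if both parents participated) per LGA to have equal chance of being allocated" to one of the three conditions. A single participating parent is therefore one unit, and a participating couple is also one unit with one allocation.

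Couples were sought. Under Inclusion criteria, mothers and fathers are both eligible, and partners of interested parents were sent their own information and consent form.

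The section Sample size/power calculation works in parents: "A 3-group comparative study would require a total sample of 184 participants (approximately 61 parents in each treatment condition"), and with dropout "we aimed to recruit approximately 221 parents (approximately 74 participants in each treatment condition"). It names the software and a moderate effect size. It mentions no within-family correlation or design effect.

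Under Data analysis: "A mixed-design analysis of variance (split-plot ANOVA) will be conducted to compare the intervention and control conditions (between-subjects factor") on each primary and secondary outcome, with pre, post and follow-up as the within-subjects factor. The section names no family effect, no cluster-robust error and no rule limiting the analysis to one parent per family.

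**The concern.** A split-plot ANOVA treats the subjects within each condition as independent. Its within-subjects factor deals with the correlation of one parent's scores over time. It does not deal with the correlation between two parents in one household who were placed in the same arm together.

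The article itself gives reasons to expect that correlation to be positive. Its Background links fatigue to infant night waking, child temperament and sleep, which partners largely share. Some outcomes have a shared target: the family functioning scale asks both partners about the same family.

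With positive correlation, the variance of an arm mean is larger than the ANOVA assumes, so false positives become more frequent. This bears on each intervention against waitlist and on the two intervention arms against each other. The 184 parents also carry less information than 184 independent people.

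**Working it through.** **Inputs from the article.** Three arms with equal allocation; family as allocation unit, with 1 or 2 parents each; 184 parents analysed; 80% power; p < .05 (two-sided assumed); moderate effect, with no number. The Data analysis section puts a medium effect at eta-squared = 0.06 or d = 0.5.

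**Inputs not in the article (assumed).** The share of families in which both parents take part, and the correlation rho between partners. Three settings are used: 25% and 0.2; 50% and 0.3; 100% and 0.4. For the group-by-time test, rho is the correlation of partners' changes, which may be smaller than that of their scores.

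**The plan's own figure.** No test is named for the 184, and no single reading gives it exactly:

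- Pairwise comparison, d = 0.5, normal approximation: 63 per arm, 189 in total. This is close. The exact t-test at 61 per arm gives 78.2% power.
- One-way three-group F test: 158 in total for f = 0.25 and 154 for eta-squared = 0.06 (f = sqrt(0.06/0.94) = 0.253). At 184 these give 86.3% and 87.0%.
- The F-test effect for which 184 gives exactly 80% is f = 0.231. This value is back-solved and is not in the article.

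None of these readings contains a clustering term.

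**Design effect.** DE = 1 + rho × (Σm²/Σm − 1), where m is the number of parents per family.

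- 25% couples: Σm²/Σm = (0.75 + 4 × 0.25)/(0.75 + 2 × 0.25) = 1.75/1.25 = 1.40. DE = 1 + 0.2 × 0.40 = 1.08.
- 50% couples: (0.5 + 2)/(0.5 + 1) = 1.667. DE = 1 + 0.3 × 0.667 = 1.20.
- All couples: 4/2 = 2. DE = 1 + 0.4 × 1 = 1.40.

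**True size and effective sample.** For a pairwise test, size = 2 × [1 − Φ(1.96/√DE)]. For the three-arm test (2 df), the chi-square critical value is divided by DE. Effective N = 184/DE.

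| Couples, rho | DE | Effective N | Pairwise size | Three-arm size |
|---|---|---|---|---|
| 25%, 0.2 | 1.08 | 170 | 5.9% | 6.2% |
| 50%, 0.3 | 1.20 | 153 | 7.4% | 8.2% |
| 100%, 0.4 | 1.40 | 131 | 9.8% | 11.8% |

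Simulation of the unadjusted three-group F test (20,000 runs, 62 per arm) gave 5.0% with no pairing. With half of the *parents* in couples and rho 0.3 (DE 1.15) it gave 7.8%, and with all in couples and rho 0.3 (DE 1.30) it gave 10.0%. With 5% of families as couples and rho 0.3, DE is 1.03 and pairwise size is 5.3%, which is negligible.

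**Power of the three-group F test at the effective N.**

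| DE | f = 0.231 | f = 0.25 | eta-squared = 0.06 |
|---|---|---|---|
| 1.00 | 80% | 86% | 87% |
| 1.08 | 77% | 83% | 84% |
| 1.20 | 72% | 79% | 80% |
| 1.40 | 64% | 72% | 73% |

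On the pairwise d = 0.5 reading, power goes from 78% at 61 per arm to about 70% at DE 1.20.

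**The case against.** The size of the problem rests on two quantities that the article does not give. If few couples enrolled, or if partners' changes are only weakly correlated, the test keeps nearly its nominal level. The article is also a condensed account, and it could be said that the handling of partners belongs in a fuller analysis plan.

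The first part stands and limits the conclusion. A reader might infer that every between-arm test exceeds 5%. The documents do not support that: it needs enrolled couples and a positive correlation for each outcome, and neither is reported. The second part carries less weight. The article does not leave the method open; it names one whose two factors do not fit the allocation unit it describes.

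A reader might also infer that power is overstated as a matter of fact. That does not follow. On the article's own medium benchmark for eta-squared, 184 has a margin that roughly absorbs a design effect of 1.20. The fall to 72% needs the back-solved f of 0.231, although the pairwise reading would also support a loss.

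Finally, it is tempting to say that partners share one workbook or home visit. The intervention sections do not say so, and the point does not need it, because the shared allocation is enough.

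**Conclusion.** The point holds in conditional form. The article allocates families, counts parents, and names an analysis without a family term. Where couples enrol and partners' outcomes or changes correlate positively, the named test is anti-conservative. Over the three assumed settings, a nominal 5% pairwise test has a true size of about 5.9% to 9.8%, with 7.4% in the middle, and close to 5% if couples are rare. These figures depend on an assumed couple share and correlation, and on two-sided testing.

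The effective sample is below 184 under the same conditions. Whether power falls below 80% cannot be settled without the effect size and test behind the 184.

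**What to change.** Replace the split-plot ANOVA with a linear mixed model that has a random family effect and parent nested in family for the repeated measures. GEE with robust errors clustered on family is an alternative. Apply it to all parent-reported outcomes, and report the number of families as well as parents in each arm.

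Restate the power with the design effect 1 + rho × (Σm²/Σm − 1), giving the assumed couple share and rho and the effect size and test used. For scale, keeping the information of 184 independent parents at DE 1.20 would need 184 × 1.20 = 221 analysed parents.

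The cost is small. Recruitment is complete but data collection was still under way, so only the analysis wording changes, and family membership should be known because families were what was allocated. Standard errors will be slightly larger and the stated power may be less favourable. If few couples enrolled, the results will hardly move.

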### Intervention

#### Written information condition

Parents allocated to the WAP written information group were sent the WAP intervention workbook. The 44-page workbook is broken into four parts designed to be used in a self-directed manner over a period of 4-weeks. The first part provides information about fatigue and exhaustion, including what it is, how it can affect parents, and why it occurs. The second part provides tips for charging up and includes strategies such as taking time out for self, helpful thinking, sleeping better and resting, eating well, and keeping active. The third part provides tips for saving energy and includes strategies such as prioritising, problem solving, and getting support. Throughout these sections of the workbook are activities to help parents think about ways to apply the strategies and make them relevant to their individual needs. The notion of developing a goal and plan to make it happen is also emphasized. The final part of the workbook then provides advice on how to make the plan work and contact information and websites for additional support services parents may choose to pursue.

#### Written information with telephone support condition

Participants in this arm received professionally-led, structured guidance to supplement the written information provided in the WAP booklet, over the four weeks of the programme. Parents received an initial home visit from a trained facilitator. The purpose of the home visit was to establish rapport with the parent, provide a WAP workbook, introduce the program and work through the first section of the workbook. At the home visit, three telephone sessions were scheduled at weekly intervals for the following three weeks, corresponding with one per session of the workbook. During the telephone sessions, the facilitator checked the parent’s understanding of the workbook content, clarified any information, answered questions, or guided progress through the material when necessary. Parents were encouraged to think about specific strategies relevant to their needs, to address barriers to these strategies, to develop goals, and ultimately, devise a plan to support them with the management of fatigue.

#### Waitlist control condition

Parents allocated to the waitlist control group initially received no intervention or resources from the research team. These families continued to receive the usual assistance and advice provided to all parents of newborns, via usual contact with MCHNs and other health professionals. Once the final follow-up questionnaire was received by the research team from parents in the waitlist control group, they were offered the WAP intervention and had the choice of receiving written information only or written information with telephone support.

### Measures

#### Demographic questionnaire

Information about parent age, gender, marital status, educational background, employment status, and demographic information about other children in the family were collected. The *Australian Bureau of Statistics, Socio-economic Indexes for Areas*[49] was used to identify families’ socioeconomic status based on their postal code. The Index of Relative Socioeconomic Disadvantage was used and is based on variables such as low income, low educational attainment, and high unemployment from the 2001 population census data. High scores reflect an area of relatively better economic status.

#### Primary study outcome

Primary study outcomes are parent-reported symptoms of fatigue, assessed at baseline and at short- (2 weeks) and longer-term follow-up (eight weeks).

*Fatigue Assessment Scale (FAS)*[50] is a ten item measure that will be used to assess the physical and cognitive symptoms of fatigue. The items are rated on a 5-point scale, ranging from 1 = *Never* to 5 = *Always*, with higher scores indicating higher levels of fatigue. The scale is reported to have good psychometric properties, and has been evaluated for use with parents
[35].

*Fatigue Severity Scale*[51,52] assesses fatigue intensity and functional limitations caused by fatigue. The nine items (e.g., “Fatigue interferes with my work, family, or social life”) are rated on a 7-point scale, ranging from 1 = *Strongly Disagree* to 7 = *Strongly Agree*. Higher scores reflect higher levels of fatigue.

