### Hypotheses

Firstly, we hypothesised that compared to a waitlist control condition, parents receiving either form of the intervention will report the following short-term outcomes at 2-weeks post intervention:

a) Stronger beliefs and intention about engaging in self-care behaviour.

b) Higher levels of self-care behaviour.

c) Lower levels of fatigue and daytime dysfunction.

d) Lower levels of irritability, improved vigour and clarity of thought.

e) Improved sleep quality.

f) Lower levels of parenting stress and parenting hostility, and higher levels of parental warmth.

Secondly, we hypothesised that compared to a waitlist control condition, parents receiving either form of the intervention will report the following longer-term outcomes at 6-weeks post intervention:

a) Higher levels of parental self-efficacy.

b) Lower levels of depression, stress and anxiety.

c) Higher quality of the couple relationship and parent–child interactions.

Finally, we hypothesised that compared to the written information only condition, the intervention effects will be significantly stronger for parents in the written information with telephone support condition.

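### The primary outcome is two unranked fatigue scales at two follow-ups, while power and the fatigue hypothesis cover 2 weeks only; no scale, visit or arm contrast is named as decisive

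*Protocol article*

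**What the plan says.** All references are to the protocol article.

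- **Primary study outcome.** The plural is used and two follow-ups are included: "Primary study outcomes are parent-reported symptoms of fatigue, assessed at baseline and at short- (2 weeks) and longer-term follow-up (eight weeks". Two instruments follow. The FAS "is a ten item measure that will be used to assess the physical and cognitive symptoms of fatigue", and the Fatigue Severity Scale "assesses fatigue intensity and functional limitations caused by fatigue". Neither scale and neither visit is ranked first.
- **Sample size/power calculation.** The total of 184 (about 61 per arm) is set for "80% power to detect a statistically significant finding at *p* < .05" and "a moderate effect size for the short-term outcomes at two weeks post-intervention". The later visit is not powered.
- **Hypotheses.** "Lower levels of fatigue and daytime dysfunction" is item c of the 2-week list. The longer-term list covers self-efficacy, depression, stress and anxiety, and couple and parent–child relationships, but not fatigue. The hypotheses compare either form of the programme with waitlist, and telephone support with written information only.
- **Randomisation.** Three arms, with "equal chance of being allocated to either of the intervention conditions (i.e., written information with telephone support or written information only) or control condition".
- **Data analysis.** One split-plot ANOVA per primary and secondary outcome, with condition between subjects and the three assessments within subjects. No follow-up contrast is named.

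**The concern.** A fatigue difference at the later visit is primary in one section, unpowered in a second and not hypothesised in a third. The hypotheses also need arm-specific answers that an omnibus ANOVA cannot give by itself, so pairwise contrasts must follow. The article does not say which scale, visit or contrast carries the conclusion.

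The stake is the meaning of the 5% level in the power statement. It fits a single decisive test, whereas the primary definition admits several. A positive finding on one scale at one visit could then be reported as a primary result with a real error rate above 5%, and readers could not tell whether that result was the one planned.

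**Working it through.** **1. The plan's own figure.** The power paragraph gives no number for a moderate effect. Data analysis gives d = 0.5 as medium, alongside "0.01, 0.06 and 0.14 as small, medium and large effect sizes" for η². For a two-sided pairwise comparison at d = 0.5:

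n per arm = 2(1.96 + 0.84)² / 0.5² ≈ 62.8, so 63 per arm and 3 × 63 = 189 in total.

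This is within 3% of 184. Power at 61 per arm is 78.9% (normal) or 78.2% (t test), against the stated 80%. The sample size is therefore consistent with **one** pairwise contrast at 5% on one outcome at one visit. An omnibus test at f = 0.25 (my assumption for that route) would need only 158.

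**2. Count of possible primary comparisons.**
- One omnibus test per scale: 2.
- Both scales, 2 weeks only, each programme v control: 2 × 2 = 4.
- Both scales, both visits, each programme v control: 2 × 2 × 2 = 8.
- Adding telephone support v written only: 2 × 2 × 3 = 12.

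**3. Chance of at least one false positive when no arm differs.** With independent tests, 1 − 0.95² = 9.8% for 2 tests and 1 − 0.95⁸ = 33.7% for 8. The real tests are correlated, so I simulated three independent arms of equal size with standardised mean scores on 2 scales × 2 visits. The same correlation r was used between scales and between visits (r² across both). Pairwise z = (difference of two arm means)/√2, two-sided at 1.96; omnibus χ² on 2 df at 5.99. The values of r are assumptions.

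| Reading | r = 0.5 | r = 0.7 |
|---|---|---|
| One omnibus test per scale (2) | 9.1% | 8.5% |
| 2 weeks only, v control (4) | 16% | 15% |
| Both visits, v control (8) | 28% | 24% |
| The same 8, favouring an intervention only | 14% | 12% |

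Every reading exceeds 5%. Settling the visit but not the scale or the contrast still leaves about 15–16%.

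**4. Keeping everything primary with Bonferroni.** For 8 tests α = 0.05/8 = 0.00625. Power at 61 per arm and d = 0.5 falls to 49%, and 80% power needs about 105 per arm (3 × 105 = 315) against 184.

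**5. One endpoint with an omnibus gate.** Simulated error rate with no arm difference: 5.0%. If exactly two arms are equal, only one pairwise null hypothesis is true and it is tested at 5%, so the family-wise rate still holds. Power for a contrast with d = 0.5 at 61 per arm, F on 2 and 180 df:
- Both programmes at d = 0.5: non-centrality 61 × (0.5²) × 2/3 = 10.2. Pairwise power 78–79% ungated, 74% gated.
- Other programme at d = 0.25: non-centrality 61 × 0.125 = 7.6. Gated power about 67–68%.

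These figures treat parents as independent and use no baseline adjustment.

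**The case against.** A reader might infer that success can be claimed from any of 8 to 12 tests, each at p < .05, with a false-positive rate of roughly 24–36%. The article does not support that, for four reasons.

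- The only stated analysis is one ANOVA per outcome, with time as a factor inside the model. Read literally, that is two primary omnibus tests, and the rate is about 8–9%.
- The 5% level appears only in the power paragraph and is attached to no contrast.
- There is no success rule. Contrast order and alpha allocation may stand in the full protocol or analysis plan, neither of which is shown, so their absence here proves nothing.
- Four of the 12 contrasts compare the two programme forms and cannot show benefit over usual care. Of the 8 that can, only those favouring an intervention support such a claim, which gives 12–14%.

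It can also be said that powering one visit while measuring a later one is no contradiction, and that neither the power nor the hypothesis section names a rival primary endpoint. Both points are fair. What remains is that the article itself defines the primary outcome, does so with two scales and two visits, and then supports only one of those visits elsewhere. An unseen analysis plan could add a testing order, but it would not make these sections agree.

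**Conclusion.** The point holds as a mismatch between sections. Primary status is given to two unranked scales at two visits, while power and the fatigue hypothesis stop at 2 weeks, and no scale, visit or contrast is decisive. The excess over 5% is modest on the literal reading (about 8–9%) and reaches 24–28% only if all 8 contrasts against control were each tested at 5%. That upper figure is a bound on what the definition allows, not a description of the plan. All rates rest on assumed correlations of 0.5 to 0.7, two-sided tests and independent parents. The mismatch itself rests on the text alone.

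**What to change.** Reconcile the Primary study outcome, Sample size, Hypotheses and Data analysis sections:

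1. Name one primary endpoint at the powered visit, 2 weeks post-intervention. FAS total is a reasonable choice because the article says that scale has been evaluated with parents. The article does not say the other scale has not, so the investigators may prefer it if they give a reason.
2. Make the other scale and the later fatigue score secondary. State the later visit consistently: the primary outcome section gives eight weeks, while the Abstract, Procedures and Hypotheses give six.
3. Test the three arms jointly at 5% on the primary endpoint, then the three pairwise contrasts at 5% each only if the joint test is significant. The split-plot ANOVA can stay for the secondary time-course results.

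**Cost.** This is more than a wording change. Recruitment is complete, data collection is under way and allocation is known to families and staff. It therefore needs a dated, justified amendment, decided before analysis and without sight of outcomes by arm, and the registry entry should be checked against it. A result seen only on the other scale or only at the later visit can no longer be called primary. The gate lowers pairwise power at 61 per arm and d = 0.5 from about 78–79% to 74%, or to about 67–68% if the other programme arm has d = 0.25. The amendment should state this. No larger sample is needed to hold the error rate.
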